### Statistical analysis

2.9.

Statistical analyses will be based on a mixed general linear model design with the two-level between group factor intervention (intervention vs. control group) and the three-level within group factor time (assessments at T0, T1 and T2) for primary and secondary outcome measures to account for both hypotheses tested in this study. A multilevel approach including study centers with their, presumably, differing TAU interventions, is not feasible due to too low a number of study centers at this hierarchical level. However, as discussed below, study centre and TAU interventions will be used as covariates and for exploratory analyses. For the first research question, the interaction between groups and time will be analysed to determine whether PTSD symptom severity differs for the intervention group after receiving the add-on treatment. For the second research questions, sleep disturbance before the intervention will be used to predict PTSD symptom severity at first and second follow-up for both groups. Due to the exploratory nature of this study, analysis will be conducted both with an intention-to-treat and a per-protocol approach, allowing for a comparison of both effect estimates (Gupta, 2011). For intention-to-treat analysis, dropouts will be included with a last observation carried forward strategy. Extreme cases and outliers will be checked for validity and excluded for per-protocol analysis if indicated. Dropouts will be reported with time point and reason in the final results. We intend to include age, gender, severity of trauma (indicated by classification in type-1 and -2 traumata), number of previous traumatic events, content of trauma-related outpatient treatment sessions and recruiting centre as covariates and in further exploratory analyses. Despite our efforts to proactively reduce variance in trauma treatment among participating trauma centers by organizing joint supervisions, we assume there will be left some significant variance that has to be considered in the statistical analyses. The content of trauma-related outpatient treatment sessions will be classified into trauma-focused versus non-trauma-focused therapy elements since it has been shown that in symptomatic acutely traumatized individuals this may cause a significant difference in treatment outcome (Roberts et al., 2019). Furthermore, we will survey whether sleep interventions have been included in the therapy process or not. By this, we intend to control for the most relevant confounding factors arising from between-participant-treatment-differences.

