### Research questions

1.4.

We therefore want to investigate whether a digital cognitive behavioural therapy for insomnia (dCBT-I) intervention delivered as an add-on to treatment as usual (TAU) can reduce trauma-related symptoms (specific PTSD symptoms as well as related symptoms such as depression, anxiety and functional outcomes) and the risk to develop PTSD in acutely traumatized individuals. Moreover, in an attempt to replicate previous findings, we will examine whether sleep disturbances pre therapy predict the development of later PTSD symptoms in this heterogeneous sample of acutely traumatized patients. More specifically, in line with previous studies we expect that measures of sleep continuity such as sleep efficiency and nightly awakenings will be especially indicative. They have lately been implicated in predicting PTSD symptoms in an EMA study (Schenker et al., 2023) and could indicate less deep, disturbed sleep and thus worse trauma memory processing (Kleim et al., 2016).

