#### Primary outcome measures

2.8.1.

The primary outcome measures are PTSD symptom severity and number of participants with probable PTSD according to a PCL-5 cut-off of 33, which showed the best sensitivity-to-specificity-ratio for detecting PTSD (Weathers et al., 2013). Due to the online-design, we could not use CAPS interview as Pigeon et al. (2022) did to survey PTSD symptom development and decided to use PTSD Checklist for DSM-5 (PCL-5; Weathers et al., 2013) and Post-traumatic Cognitions Inventory (PCTI; Foa et al., 1999) as self-reports instead, both applied at T0, T1 and T2. Whereas the PCL-5 covers all PTSD symptoms, PTCI specifically measures trauma-related cognitions. The PCL-5 asks respondents to rate bothering of PTSD symptoms during the past month on a 5-point likert scale (1 = not at all to 5 = extremely) and has strong internal consistency (*α* = .94), test–retest reliability (*r* = .82), and convergent (*rs* = .74 to .85) and discriminant (*rs* = .31 to .60) validity (Blevins et al., 2015). The PTCI consists of 33 questions about trauma-related cognitions (based on the three factors Negative Cognitions About Self, Negative Cognitions About the World and Self-blame) which respondents rate on a 7-point-likert scale (absolutely no consent to strong consent). As PCL-5, PTCI shows excellent psychometric properties with internal consistency ranging from *α* = of .86–.97 (Foa et al., 1999). As the PCL-5 contains the item ‘Trouble falling or staying asleep?’ (Weathers et al., 2013), all analyses for the PCL-5 will be conducted with and without this item separately to detect whether potential changes on this measurement are solely driven by changes in sleep quality.

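### The second research question predicts later PTSD severity from pre-intervention sleep, but T0 PCL-5 is not among the listed covariates, so an association cannot be told apart from baseline severity persisting

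*Protocol article*

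**What the plan says.** The aim in section 1.4 (Research questions) is about the course of symptoms: "we will examine whether sleep disturbances pre therapy predict the development of later PTSD symptoms". The analysis in section 2.9 (Statistical analysis) is about their later level: "sleep disturbance before the intervention will be used to predict PTSD symptom severity at first and second follow-up for both groups".

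The covariates are named in the same section: "We intend to include age, gender, severity of trauma (indicated by classification in type-1 and -2 traumata), number of previous traumatic events", followed by "content of trauma-related outpatient treatment sessions and recruiting centre as covariates and in further exploratory analyses". T0 PCL-5 is not in this list, although section 2.8.1 says of the PCL-5 and the cognitions inventory that they are "both applied at T0, T1 and T2".

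Three other statements bear on the point:

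- The general model is a mixed linear model with group and a "three-level within group factor time (assessments at T0, T1 and T2) for primary and secondary outcome measures to account for both hypotheses".
- Section 2.8.1 deals with the sleep item inside the PCL-5: "all analyses for the PCL-5 will be conducted with and without this item separately".
- For the intention-to-treat analysis, "dropouts will be included with a last observation carried forward strategy".

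**The concern.** Every participant enters with PTSD symptoms above the PCL-5 cut-off, so a claim about how symptoms develop needs the starting level. Section 1.2 describes sleep disturbance as prominent in the diagnostic criteria for PTSD, so a positive T0 correlation between sleep disturbance and PCL-5 is to be expected. Some persistence of T0 severity is also to be expected; section 2.8.1 reports a PCL-5 test-retest correlation of .82, with no interval given.

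If both links are positive, pre-intervention sleep will correlate with later PCL-5 even when it carries no information beyond T0 severity, and the correlation will have the sign of the hypothesis. What is at stake is whether a positive answer to the second research question can be read as evidence about sleep.

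**Working it through.** **1. The plan's own figure.** Section 2.4 gives N = 86 for f = .25, 80% power and alpha 5%. For a between-group effect with m = 3 assessments and an assumed within-person correlation of .5 (not stated), lambda = f² × N × m / (1 + (m − 1) × .5) = .0625 × 86 × 3 / 2 = 8.0625. With 1 and 84 degrees of freedom the power is .801, so 86 is reproduced. This sizes the group comparison. No figure is given for the second research question, and N = 86 is used below as its analysed size.

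**2. Induced correlation.** Let a be the correlation of T0 sleep disturbance with T0 PCL-5, and b that of T0 with later PCL-5. Neither is in the documents; both are assumptions. If sleep adds nothing once T0 PCL-5 is known, its correlation with later PCL-5 is a × b. For .4 and .5 this is .20.

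**3. False-positive rate without adjustment.** By Fisher's z at N = 86, atanh(.20) × √83 = .2027 × 9.110 = 1.847, and P = Φ(1.847 − 1.960) = .455. A simulation (6,000 runs per cell, two-sided 5%) agrees:

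| a | b | a × b | Fisher z | Simulated, unadjusted | Simulated, T0 PCL-5 as covariate |
|---|---|---|---|---|---|
| .2 | .3 | .06 | 8.5% | 8.2% | 4.6% |
| .3 | .5 | .15 | 28.0% | 27.7% | 5.2% |
| .4 | .5 | .20 | 45.5% | 44.6% | 5.2% |
| .5 | .5 | .25 | 64.3% | 64.5% | 5.2% |
| .6 | .7 | .42 | 98.3% | 98.4% | 4.8% |

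By Fisher's z, the pair .5 and .6 (product .30) gives 80.5%. Over all simulated cells, including those with carry-forward, the adjusted rate is 4.6% to 5.5%.

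**4. Carry-forward.** Suppose 20% of 104 participants leave before T1, so that their T0 score becomes the later outcome, and the score has the same mean and variance at each time. The induced correlation becomes a × (.8 × b + .2) = .4 × (.4 + .2) = .24. Then atanh(.24) × √101 = .2448 × 10.05 = 2.460, and P = Φ(.500) = 69% (simulated 69.5%). Part of the rise from 45% is the larger N: a correlation of .20 at N = 104 gives Φ(2.037 − 1.960) = 53%. Carry-forward accounts for the step from 53% to 69%. Those who leave between T1 and T2 carry T1 forward instead, so the effect on T2 would be smaller.

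**5. Does T0 as a level of the time factor help?** A sleep main effect over T0, T1 and T2 contains the cross-sectional T0 association. A sleep-by-time term tests change. Under the same null its correlation is a × (b − 1) / √(2(1 − b)) = .4 × (−.5) / 1 = −.20, and in simulation it rejects in 46.7% of runs with a negative sign. Neither form replaces T0 PCL-5 as a covariate.

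**6. Range restriction.** Suppose the values .4 and .5 hold before selection and entry truncates a normal T0 PCL-5. With variance ratio u², each correlation r becomes r × u / √(1 − r² + r² × u²).

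- Truncation at the median (u² = .363): .254 and .329, product .084, rate 12%.
- Truncation 1 SD below the mean (u² = .630): .327 and .417, product .136, rate 24%.
- For .5 and .6 the rates are 24% and 50%; for .3 and .4 they are 7% and 11%.

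**The case against.** **The document does not fix the model.** Section 2.9 gives this question one sentence and no equation. The covariate list is for the whole trial, is worded as an intention and is not called exhaustive, and the mixed model already holds T0 as an outcome level. A reader might infer that the plan rules out baseline adjustment; it does not. What stands against the objection is that a list was written out, the one variable this question most needs is absent, and T0 as an outcome level does not do the same work (step 5).

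**The size is not known.** A reader might infer that the second aim would very likely be declared confirmed whatever sleep does. The documents do not support that: the correlations are assumptions, the middle case is below even odds without carry-forward, the low case is near nominal, and the PCL-5 entry cut-off probably lowers both correlations. The requirement that sleep disturbance arose or worsened after the trauma may narrow the sleep measure too. This part of the objection stands.

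**Adjustment narrows the question.** T0 symptoms are measured up to three months after the trauma and may already reflect disturbed sleep, so conditioning on them can remove part of the effect of interest. That is a fair reason to keep the unadjusted estimate as well, but not to let it alone carry a claim about development.

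**The sleep item is already handled.** Analyses with and without it are planned, so its presence is not a separate defect. Removing it leaves shared baseline severity untouched, and also leaves overlap such as bad dreams, which the sleep-quality addendum covers and section 1.1 counts among core PTSD symptoms.

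**Conclusion.** The point holds as a gap in the stated analysis of the second research question. As written, the test mixes sleep with baseline severity, and carry-forward strengthens the mixing. The direction follows whenever both correlations are positive. The size is conditional: at N = 86, if sleep adds nothing beyond T0 severity, about 8% to over 80% false positives across the assumed range, about 45% at .4 and .5, and 12% or 24% for that same pair under the two truncation illustrations, against about 5% with adjustment. How likely a false confirmation is in this trial cannot be determined from the documents. The question is secondary in a study that describes itself as exploratory, and the randomised group comparison is unaffected. This should be corrected, but it does not threaten the trial's main result.

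**What to change.** State in section 2.9 that the models for the second research question include T0 PCL-5 and treatment arm as covariates. Compute T0 PCL-5 without the sleep item when the outcome excludes it. Make this the main estimate for symptom development and report sleep's incremental R-squared. Report the unadjusted association alongside, labelled as crude prognosis, because T0 symptoms may partly reflect earlier sleep disturbance.

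T0 PCL-5 and arm are already recorded, so the cost is a change of wording and two model terms. The small downside is that the adjusted estimate may be conservative if T0 symptoms lie on the path from sleep to later symptoms; reporting both estimates shows by how much. No new variable is needed.

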### Post-traumatic stress disorder (PTSD) and the need for early interventions

1.1.

About 50–70% of adults worldwide experience at least one traumatic event in their lifetime, such as war events, physical or sexual violence, accidents or the unexpected death of a loved one. Such traumatic events can cause severe psychological difficulties. The majority of traumatized individuals remits spontaneously. Nevertheless, the conditional risk of PTSD, i.e. the prevalence of PTSD among those exposed to traumatic events ranges from 2.5% (Italy) to 17.6% (Northern Ireland) (Atwoli et al., 2015) with a subgroup of them experiencing the full symptoms of acute stress disorder before the manifestation of PTSD (Bryant et al., 2011). The core symptoms of PTSD encompass re-experiencing the traumatic event in the present (such as intrusions, flashbacks and nightmares), hyperarousal and avoidance of trauma reminders. PTSD and related disorders do not only cause significant distress and impairment of social and daily functioning but may even increase the risk of chronic physical illness (Scott et al., 2013). During the past decades, there has been an increasing effort to develop early psychological interventions aiming to prevent the onset of PTSD. According to the definition from the German guidelines for diagnostics and treatment of acute trauma, all interventions aiming at making the experience more apprehensible and reducing the risk of trauma sequela delivered within the first three months after trauma experience are referred to as early interventions (Bengel et al., 2019). These guidelines recommend early trauma-focused CBT (TF-CBT) for those who exhibit clinical symptoms of post-traumatic stress and active monitoring for those who display subclinical symptom burden (Bengel et al., 2019). However, trauma-focused early interventions are not accessible for the majority of traumatized individuals which increases the risk of manifestation of trauma-related symptoms. In search for feasible early interventions, researchers started to focus on the cognitive and emotional mechanisms that are known to be relevant in the context of PTSD development.

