### Participants

2.3.

Participants aged between 18 and 55 years will be included in the study if they (1) have experienced a traumatic event within the past three months as measured with Life Events Checklist (LEC-5; Weathers et al., 2013) and show PTSD symptoms (PTSD Checklist for DSM-5 (PCL-5) score above cut-off value of 33) and (2) report on sleep disturbances which evolved or became stronger after the traumatic experience. Participants will be excluded from the study if they (1) take benzodiazepines or benzodiazepine receptor agonists, (2) report on a lifetime diagnosis of psychosis, bipolar disorder or more than two episodes of major depression, (3) have suffered from an alcohol or substance use disorder within the past year, (4) have an IQ < than 80 points, (5) are diagnosed with any systemic or neurological disorder (e.g. dementia), (6) show signs of acute suicidality, (7) are insufficiently able to communicate in German, (8) work in shifts or have had an intercontinental flight crossing two or more time zones within the past 30 days or (9) suffer from sleep apnea.

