### Sample size

2.4.

The planned sample size is based on calculations in G*Power 3.1.9.7 (Faul et al., 2007). Literature investigating the effect of combined sleep- and trauma-focused therapy on trauma-related symptoms is scarce. Pigeon et al. (2022) report a medium sized effect of CBT-I on trauma-related symptoms measured with the Clinician Administered PTSD Scale (CAPS; Blake et al., 1995) in individuals diagnosed with PTSD after having experienced a traumatic event within the past year. Referring to this finding and being interested in a clinically relevant effect, we chose an effect size of Cohen's *f* = .25 as a basis for power analysis and sample size calculation. Calculations setting the desired power to 80% and the risk of Type I error rate to *α* = 5% resulted in a required sample size of *N* = 86 to be able to detect medium sized between factor effects in a mixed design, provided the assumed effects exists in the investigated population. Considering a dropout rate of 20% from guideline-recommended psychological treatments for post-traumatic stress disorder (Varker et al., 2021) as an orientation for potential attrition rate, we intend to recruit *N* = 52 participants per group. Due to the exploratory nature of this pilot study, we used only our primary outcome measure for sample size calculations.

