#### Intervention group

2.6.1.

Participants in the intervention group will get access to the sleep app *somnio* which serves as the form of dCBT-I employed in this study. *Somnio* is the first digital health application listed permanently with the German Federal Institute for Drugs and Medical Devices for the treatment of insomnia and therefore approved for prescription by medical doctors and psychologists since 2020 (mementor DE GmbH, Leipzig, Deutschland). It belongs to the best rated dCBT-I (Simon et al., 2023) and has been shown to significantly and long-lastingly improve insomnia (Lorenz et al., 2019; Maurer et al., 2023), as well as epiphenomena such as daytime functioning, quality of life, symptoms of depression and anxiety (Schuffelen et al., 2023). Compliance data and completion rates of 68% are promising as well for *somnio*, even in a heterogeneous real-world sample (Schuffelen et al., 2023) which is indeed slightly lower than some reported compliance rates for CBT-I that is delivered in person. However, with 48–91% there is also a wide range of compliance rates in this intervention type (Mellor et al., 2022) and *somnio*'s data fall completely within that range. One activation code is valid for 90 days and users can access the application via app or web browser. The intervention period for this respective study is planned for approximately 8 weeks. The intervention program consists of 10 educative core- and 6 concomitant-modules which are based on Morins microanalytic model of insomnia (Morin, 1993a). In this model, it is stated that insomnia is primarily sustained by a cycle of self-perpetuating factors such as high arousal, negative consequences, maladaptive habits and dysfunctional cognitions about sleep (Perlis et al., 2005). Users are guided through the intervention program by an animated sleep coach called Albert to create a tailored dialogue that is based on pre-programmed input by CBT-I experienced psychotherapists. A list and description of all educative modules and the closing session can be found in Table 1.

**Table 1. T0001:** Content of dCBT-I application somnio.

Module	Content description
Introduction	Introduction to therapy content and procedure, personalization of settings, recording of sleep symptoms and therapy goals
Sleep diary	Introduction to sleep diary as basis for subsequent personalized training and instructions on how to fill in the reports

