Apart from considerations around the study design, there are some methodological limitations. First, the sleep intervention being delivered in digital format forces the participants to process the intervention content self-reliantly. This may lead to decreased compliance compared to in-person interventions, where therapists can directly address compliance. As we have access to app use and sleep diary data however, we are able to measure participation in the intervention and control group. Second, and related to patient compliance is the self-selection of more motivated and possibly also less severely impaired patients in the CBT-I group. To take this into account we will conduct an intent-to-treat analysis, and we will analyse characteristics of all dropouts to detect potential differences between both groups. Third, beside of sleep questionnaires indicating subjective sleep quality we decided to not include any objective sleep measurements. Thus, changes in sleep architecture that might be related to potential changes in trauma processing cannot be detected. For this first exploratory study, it is more important for us to include a high number of patients at different centres within a reasonable period of time to uncover possible effects of CBT-I at the behavioural level. If this approach is successful, objective sleep data should also be collected in subsequent studies to investigate underlying mechanisms.

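### Last observation carried forward is the only rule for dropouts in the intention-to-treat analysis, and in a population expected to improve it distorts the PCL-5 treatment effect by an amount and in a direction that depend on dropout in each arm

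*Protocol article*

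**What the plan says.** Protocol article, Statistical analysis (2.9): "For intention-to-treat analysis, dropouts will be included with a last observation carried forward strategy". The section names no other way of handling missing outcomes. It plans intention-to-treat and per-protocol analyses side by side, labels neither as the main one, and uses three assessments: T0, T1 and T2 (six months after baseline).

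Other statements that bear on this rule:
- Section 1.1, on expected course: "The majority of traumatized individuals remits spontaneously".
- Participants (2.3): entry within three months of the trauma, with a PCL-5 "score above cut-off value of 33".
- Primary outcome measures (2.8.1): PTSD symptom severity and "number of participants with probable PTSD according to a PCL-5 cut-off of 33".
- Sample size (2.4): "Considering a dropout rate of 20% from guideline-recommended psychological treatments for post-traumatic stress disorder". No figure is given by arm.
- Discussion (3): a possible "self-selection of more motivated and possibly also less severely impaired patients in the CBT-I group", followed by "To take this into account we will conduct an intent-to-treat analysis".

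**The concern.** Carrying the last value forward is right only if the average change that dropouts undergo after their last visit is zero, or happens to balance between the arms. The protocol gives reasons to expect otherwise: recent trauma, usual treatment in both arms, and a natural course that for most people is improvement.

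With one baseline and two later visits, a participant lost before T1 enters both later time points at the T0 score. One lost between T1 and T2 is fixed at T1. The entry threshold is also the cut-off of the binary outcome, so most early dropouts are classified as probable PTSD whatever happened to them.

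Both PCL-5 primary outcomes are affected. The intention-to-treat analysis is also the named safeguard against selection in the dCBT-I arm, so a rule that adds its own bias there weakens what the protocol relies on.

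**Working it through.** **The plan's own figure.** For a between-group effect in a repeated-measures design, λ = f²·N·m / (1 + (m−1)ρ). With f = 0.25, N = 86, m = 3 and ρ = 0.5 (ρ is not stated and is assumed), λ = 0.0625 × 86 × 3 / 2 = 8.06, and F(1, 84) gives power 0.801. The stated N = 86 reproduces, so the sample-size calculation is not the source of this problem.

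**Inputs.** From the protocol: 52 per arm, 20% dropout overall, three visits. Assumed, because the protocol does not give them: PCL-5 SD 15, T0–T2 correlation 0.5, control-arm improvement R = 15 points (range 10–20), true extra benefit D = 7.5 points (half an SD), dropout by arm (dI in dCBT-I, dC in control), all dropout before T1 and unrelated to outcome. Improvement is counted as positive.

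**Formula.** Dropouts are entered with zero change, so the expected effect is (1−dI)(R+D) − (1−dC)R = (1−dI)D − (dI−dC)R. The first term is shrinkage. The second is bias from unequal dropout.

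**Mean PCL-5 effect, true value 7.5:**

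| Dropout dCBT-I / control | Arithmetic | Result |
|---|---|---|
| 20% / 20% | 0.80 × 7.5 − 0 | 6.0 |
| 24% / 16% | 0.76 × 7.5 − 0.08 × 15 | 4.5 |
| 16% / 24% | 0.84 × 7.5 + 0.08 × 15 | 7.5 |
| 20% / 32% | 0.80 × 7.5 + 0.12 × 15 | 7.8 |
| 10% / 30% | 0.90 × 7.5 + 0.20 × 15 | 9.75 |

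For 24%/16%, R = 10 gives 5.7 − 0.8 = 4.9 and R = 20 gives 5.7 − 1.6 = 4.1. With more dropout in control the two terms work in opposite directions. At 16%/24% they cancel (0.16 × 7.5 = 0.08 × 15 = 1.2). The effect is inflated only when (dC−dI)R exceeds dI·D.

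**Power at 20%/20%, t test on change at T2.** The SD of change is 15 × √(2 × (1 − 0.5)) = 15.
- Carried forward: the variance is 0.8 × 225 + 0.16 × 22.5² = 261 in dCBT-I and 0.8 × 225 + 0.16 × 15² = 216 in control. SE = √((261 + 216)/52) = 3.03, and 6.0/3.03 = 1.98, so power is about 0.51.
- Observed data only: 52 × 0.8 = 41.6 per arm, SE = 15 × √(2/41.6) = 3.29, and 7.5/3.29 = 2.28, so power is about 0.62.

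Simulation agrees (0.49 to 0.51 against 0.61 to 0.62). At 24%/16% it gives 0.31 against 0.61.

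**No true effect.** Equal dropout gives no bias and about 5% rejection. At 24%/16% the bias is −0.08 × 15 = −1.2 points. At 30%/10% it is −0.20 × 15 = −3.0 points (−2 to −4 for R = 10 to 20), with rejection 0.24 in a simulation using SD 12.

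**Probable PTSD.** Assume true rates of 30% in dCBT-I and 50% in control, and count every early dropout as a case, which is the extreme. The true difference is −20 percentage points.
- 20%/20%: (0.20 + 0.80 × 0.30) − (0.20 + 0.80 × 0.50) = 0.44 − 0.60 = −16 points.
- 24%/16%: (0.24 + 0.76 × 0.30) − (0.16 + 0.84 × 0.50) = 0.468 − 0.58 = −11.2 points.
- 10%/30%: 0.37 − 0.65 = −28 points.

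**The case against.** The strongest case on the other side has several parts.

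- **Dropout by arm is unknown.** A reader might take the sentence "Compliance data and completion rates of 68% are promising as well" in the Intervention group section (2.6.1) to imply 32% dropout under dCBT-I. The documents do not support this. That figure is app completion in a real-world sample, and T1 and T2 links go to all participants whether or not they use the app. Control participants have a daily diary task for eight weeks and could be lost more often. The Discussion raises possible self-selection; it does not forecast unequal dropout. This stands: the direction of bias is open, and it would be wrong to say the rule always works against dCBT-I.
- **Dropouts may differ from completers.** In general the bias is dC·mC − dI·mI, where mI and mC are the true mean improvements of dropouts after their last visit. If they improve little, the distortion is smaller. If dCBT-I dropouts follow the control course, the average effect over all randomized participants at 20% dropout is itself 0.8 × 7.5 = 6.0, and equal dropout leaves no bias. This is fair, but it rests on unverified assumptions, and unequal dropout still biases the result whenever dropouts recover.
- **Timing.** Only losses before T1 are fixed at T0. Later losses are fixed at T1 and distort T2 by the change from T1 to T2 alone.
- **Not every early dropout must be a case.** The threshold is checked at screening and T0 follows randomization, so some T0 scores may be at or below 33.
- **Standard errors.** One might infer that filled-in values make them wrong. Under equal dropout with no effect, the model and empirical standard errors agreed at about 2.9, with 5% rejection. The excess rejection under unequal dropout comes from bias.
- **Status of the analysis.** Neither analysis is called main, the study calls itself exploratory, and the remission statement concerns traumatized people in general. Yet the trial is powered at 80% on its primary outcome, and the per-protocol comparison is itself exposed to the selection that the Discussion describes.

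**Conclusion.** The concern holds in limited form. The rule is stated in the protocol and conflicts with the course the protocol itself expects. If dropout is early and unrelated to outcome, equal 20% dropout shrinks a true effect by about a fifth and costs roughly 0.12 in power (0.50 against 0.62). A split of 24% against 16%, still 20% overall, takes 7.5 points to 4.5. The opposite split can offset the shrinkage or, if large enough, inflate the effect, so the rule cannot be defended as conservative.

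These sizes rest on assumed SD, correlation, improvement and dropout by arm; the protocol supplies only the overall 20%. What does not depend on them is that intention-to-treat with this rule fails to give the protection against selection for which it is invoked.

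**What to change.** Replace the rule in section 2.9 before outcomes are analysed.

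1. **PCL-5 score:** a likelihood-based repeated-measures model on all observed data, with T0, T1 and T2 all as outcomes, baseline means constrained equal across arms, group by time, and unstructured covariance. Everyone with at least one score then contributes. A model with only T1 and T2 as outcomes and T0 as covariate would not do, because a participant lost before T1 would have no outcome row. Multiple imputation that includes T0 is an acceptable alternative.
2. **Probable PTSD:** derive it from multiply imputed PCL-5 scores.
3. **Sensitivity:** add one delta-adjusted analysis for data missing not at random, with the shift varied by arm, so that dropouts who improve less or lose the benefit of dCBT-I are covered.
4. **Last observation carried forward:** keep it at most as a sensitivity analysis.

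The cost is analysis wording and a little more analysis work, with no new data. The main model then relies on missing-at-random, which should be stated and is what step 3 tests.
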